#### Step 3: Participation

##### Overview

Women who meet the inclusion criteria and provide consent to participate in the study are enrolled in the study. All women who decide to participate in the study will be asked to sign an informed consent after a careful explanation of the study, as described in the Participant Recruitment and Withdrawal section.

Participants will also be asked if they would like to take part in a qualitative interview 2 months after delivery. In case of positive feedback, their telephone number will be collected to facilitate future contact and follow-up interviews. Women who provide consent to this interview will be sent (again via the app) a questionnaire 1 month after the expected date of delivery in which the following will be asked: (1) actual date of delivery, (2) type of delivery, (3) sex of baby, (4) name of baby, (5) mode of breastfeeding, and (6) date and time when the woman wishes to be contacted for the interview.

As shown in Table 1, the psychoeducational intervention involves completing self-report questionnaires delivered at the beginning, during, and at the end of the interaction with ALBA, in addition to the initial screening phase. Completing the instruments takes about 20 minutes. Specifically, 5 questionnaires will be administered at the beginning and 6 at the end of the intervention to investigate stress, self-efficacy, emotional regulation, psychological flexibility, coping strategies, and psychological well-being. None of these questionnaires has diagnostic purposes, so they will not be used to make diagnoses of psychopathology but only to collect descriptive data. Women with psychopathology will be excluded a priori from participation in the study (as defined in the Participant Recruitment and Withdrawal section). Four questionnaires will be delivered during the course to assess the usability and engagement of the woman with the app and ALBA. Specifically, usability questionnaires will be offered at the end of weeks 3 and 6 (ie, the end of the study).

A detailed description of each instrument that will be administered is presented in subsequent sections.

The Coping Orientation to Problems Experienced (COPE) [51] is a shortened version of the COPE Inventory, designed to assess various coping strategies individuals use to deal with stress. This 25-item questionnaire explores strategies, such as active coping, planning, and acceptance, providing a complex picture of an individual’s coping behavior. It uses a Likert scale from 1 (never do it) to 4 (do it often), with a minimum score of 25 points and a maximum of 100. Foà et al [52] translated and validated the questionnaire in Italian, showing good psychometric characteristics.

The Emotion Regulation Questionnaire [53] is a 10-item scale designed to measure the tendency to use 2 emotional regulation strategies as cognitive reappraisal and expressive suppression. Respondents answer each item on a 7-point Likert-type scale ranging from 1 (strongly disagree) to 7 (strongly agree). Balzarotti [54] translated and validated the questionnaire in Italian, showing good psychometric characteristics. In this study, Cronbach α was 0.81 for cognitive reappraisal and 0.84 for expressive suppression.

The GHQ is a self-assessment instrument designed to identify mental health disorders and monitor general psychological well-being. Developed by Goldberg and Blackwell [55], the GHQ is widely used in clinical, research, and public health settings. The 12 items of the questionnaire are formulated to investigate how the individual has been feeling recently, with reference to psychological symptoms (such as anxiety and depression), ability to cope with everyday situations, sleep disturbances, and somatic symptoms. The response is based on a 4-point Likert scale, ranging from “much better than usual” to “much worse than usual” with a maximum score of 36. Fontanesi et al [56] translated and validated the questionnaire in Italian, showing good psychometric characteristics.

The General Self-Efficacy Scale (GSE) [57] is a psychometric instrument designed to assess an individual’s general perception of self-efficacy, that is, confidence in one’s ability to organize and perform the actions necessary to handle potentially stressful or difficult situations. It consists of 10 statements on which respondents must express their level of agreement on a Likert scale ranging from 1 (not true for me) to 4 (exactly true for me). Items on the scale explore various aspects of self-efficacy, such as problem-solving ability, overcoming obstacles, and handling unexpected situations. The total score, obtained by summing the scores of all items, reflects the individual’s overall perceived level of self-efficacy and can range from 10 to 40. The GSE scale was translated into 28 languages. Scholz et al [58] examined the instrument’s psychometric properties in 25 countries, concluding that the construct of perceived self-efficacy is international and that the GSE is an equivalent measure across different cultures. Cronbach α ranged from 0.79 to 0.90. The Italian adaptation of the GSE scale was developed by Sibilia et al [59].

The K10 is a widely used screening instrument to measure psychological distress. Developed by Kessler et al [45], the K10 is a short questionnaire consisting of 10 items that investigate the frequency of psychological symptoms experienced by the individual in the past month, such as nervousness, sadness, fatigue, and feelings of hopelessness. Each question is scored on a 5-point scale, ranging from “not at all” to “all the time.” Total scores can range from a low of 10 to a high of 50, with higher scores indicating a higher level of psychological distress. The Transcultural Mental Health Center also makes available the validated version of this questionnaire in Italian [46].

The MPFI [47] is an assessment tool that measures psychological flexibility on several dimensions. It investigates how people adapt their thoughts and behaviors in response to changing situations and challenges. The MPFI focuses on various aspects of psychological flexibility, including openness to experiences, present-moment awareness, and value-driven action. The 12 dimensions of flexibility and inflexibility (according to the hexaflex model) are assessed through 60 Likert scale items from 1 to 6. The Italian adaptation of the MPFI scale was developed by Landi et al [48].

The UES-SF [34] is a short self-report questionnaire to assess UE with a digital solution. This measure includes 12 items based on a 5-point Likert scale, ranging from 1 (strongly disagree) to 5 (strongly agree). The questionnaire consists of 4 factors: (1) focused attention, which indicates the feeling of being immersed in the interaction; (2) perceived usability, which is the negative effect experienced due to the interaction and the effort expended; (3) aesthetic attractiveness, which represents the graphical and visual appeal to a digital solution; and (4) the reinforcement factor (reward). The latter is a single factor that includes duration, which evaluates the overall success of the interaction; novelty, which examines the general interest related to the interaction with a digital solution; and, finally, the perceived engagement factor, which evaluates the overall enjoyment of the interaction. This questionnaire was not available in Italian and was, therefore, translated through the back translation procedure.

The uMARS [65] is a tool for assessing the quality and functionality of mobile apps. It is characterized by a 20-item measure that includes 4 objective quality subscales (engagement, functionality, aesthetics, and information quality) and 1 subjective quality subscale rated on a 5-point Likert scale, ranging from 1 (poor) to 5 (excellent). The total and subscales scores have very high coefficients (0.90 and 0.78-0.80, respectively). The scale has also been validated in the Italian context [66].

#### Data Analysis

##### Quantitative Analysis

Statistical data processing will be conducted using the software R (version 4.0.0; R Foundation for Statistical Computing), SPSS Statistics (IBM Corp), and Stata (version 17; StataCorp LLC).

Categorical variables will be summarized through absolute and percentage frequency distributions, and quantitative variables through appropriate centrality and variability indices.

Descriptive analyses will be calculated for both psychological variables (stress level, anxiety level, depression level, emotional regulation, psychological flexibility, coping strategies, well-being, and QoL) and variables on usability (UX) and UE. These analyses will be performed on the variables analyzed at the beginning, during, and at the end of the interaction with ALBA.

The relationships between variables will be analyzed mainly through ad hoc statistical tests, such as the chi-square test, Fisher exact test, 2-tailed *t* test for paired data, Wilcoxon nonparametric tests, and the sign test (based on assessment of compliance with assumptions), to understand the differences between the beginning and the end of the course in the same study sample with respect to the variables under investigation.

In addition, univariate logistic or multinomial regression models will be presented. Finally, to eliminate possible confounders, multiple regression models will be proposed in which the effects of the explanatory variables on the outcome variables will be adjusted for possible confounders. For each analysis, statistical significance will be found with a *P* value of ≤.05. It is also planned to use McNemar test [68] and Cochran Q [69] to evaluate paired qualitative data.

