#### Secondary Objective

The secondary objective is to assess the level of pre-post psychological well-being through administered self-report questionnaires at the beginning and the end of the intervention.

This represents a preliminary exploration of the potential impact of the intervention by assessing changes in psychological well-being through post self-report questionnaires administered at the beginning and end of the intervention. Although this does not constitute an efficacy evaluation per se, it aligns with the *refine* phase of the ORBIT model, where early signals of potential effectiveness may be explored alongside feasibility and acceptability. This preliminary assessment aims to inform the design of future pilot or randomized controlled trials.

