### Sample Size

This research project is designed as a proof-of-concept study, where a limited sample is sufficient to achieve the intended aims. It was calculated that if nonparametric statistics are conducted (assuming the distribution is not normal), the sample should consist of 24 pregnant women with Bonferroni correction (α=.025). The sample size and power for nonparametric tests (Kruskal-Wallis and Wilcoxon post hoc tests) were calculated according to method reported by Noether [33]. If parametric statistics are conducted (assuming the normal distribution), the sample should consist of 41 pregnant women with Bonferroni correction (α=.025). The sample calculation was further confirmed with the

Power Analysis and Sample Size (NCSS LLC) and Stata (StataCorp LLC) programs, for which the resulting numerosity is 41 participants, assuming null hypothesis (Ho):d=d0, alternative hypothesis (Ha):d≠d0, and considering as study parameters α=.025; mean of group 1 (ma1): 0.000; power: 0.800; mean of group 2 (ma2): 1.000; delta (difference of means, delta): 0.500; expected difference (da): 1.000; and SD of difference (sd_d): 2.000.

Thus, by a power level set at 0.80, a significance level of .025, and considering a 20% potential dropout rate, an estimated 50 pregnant women are needed for recruitment to conduct the study.

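### Pre-post inference rests mainly on complete-pair tests at P≤.05, with no interval stated for the mean change meant to inform later trials

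*Protocol article*

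**What the plan says.** The Quantitative Analysis section says that differences between the beginning and the end of the course will be examined mainly through a list of tests. For numeric scores the relevant ones are the two-tailed t "test for paired data, Wilcoxon nonparametric tests, and the sign test", chosen after checking assumptions. The decision rule is: "For each analysis, statistical significance will be found with a *P* value of ≤.05". The same section also plans descriptive summaries at each time, logistic or multinomial regressions, multiple regressions adjusted for confounders, and McNemar and Cochran Q tests.

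Under Secondary Outcome, one end point for each questionnaire is the difference in mean score between the two survey times. Table 1 places five of the six before-and-after questionnaires at week 0 and week 6. The GHQ has its first measurement at screening.

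The Secondary Objective says of the pre-post assessment: "This preliminary assessment aims to inform the design of future pilot or randomized controlled trials". The Sample Size section sets the recruitment target "by a power level set at 0.80, a significance level of .025, and considering a 20% potential dropout rate". The Results section counts statistically significant psychological improvement among the benchmarks for moving to a broader trial.

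For missing questionnaires, the article mentions reminders (Design and Study Plan) and information gathered at the later interview (Primary Outcome and Qualitative Interview). It mentions no confidence interval.

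**The concern.** Two things do not fit together.

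First, a paired t, Wilcoxon signed-rank or sign test needs both scores. A woman who gives a baseline score and then leaves adds nothing to the comparison. If leaving is related to her baseline level, the women who remain start from a different mean than the whole sample. Change normally depends on starting level, so their mean change is then shifted too. The baseline scores already collected could correct this.

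Second, someone designing the next trial needs the size of the change, its uncertainty, its SD and the correlation between the two measurements. A verdict at P≤.05 supplies none of these, yet the progression benchmark is worded in terms of significance. At stake is a secondary, exploratory estimate that will feed later sample-size work.

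**Working it through.** **1. The plan's own figure.** Inputs from Sample Size: two-sided alternative ("alternative hypothesis (Ha):d≠d0"), alpha .025, power 0.80, and "expected difference (da): 1.000; and SD of difference (sd_d): 2.000". The standardized difference is 1.0/2.0 = 0.5, which agrees with "delta (difference of means, delta): 0.500". A paired t test with the noncentral t distribution gives n = 41 with power 0.805, so the stated 41 is reproduced.

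**2. Women left in the paired tests.** 50 × (1 − 0.20) = 40, so about 10 women are lost to the comparison. With 40 pairs, power is 0.793 at alpha .025 and 0.869 at alpha .05. The loss of power against the planned 0.80 is negligible. The issue is possible bias and what is reported.

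**3. Precision of the mean change.** The 95% half-width is t(0.975, n−1) × SD of difference / √n. With SD 2.0:

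| Women with both scores | Half-width | In SDs of change |
|---|---|---|
| 40 | 0.64 | 0.32 |
| 41 | 0.63 | 0.32 |
| 50 | 0.57 | 0.28 |

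Around the expected change of 1.0, 40 completers would give an interval of roughly 0.36 to 1.64. A planner needs that range, and a P value does not show it.

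**4. Bias if dropout depends on baseline.** Nothing in this step comes from the documents except the 20%. Assumptions: logistic dropout on baseline with 20% overall, equal SDs at both times, linear dependence of the week 6 score on baseline with correlation r, and a true change of 0.5 SD. Then

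bias of completers' mean change = (r − 1) × shift in baseline mean among completers.

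Solving the dropout model numerically gives the shift when women with higher scores leave more often:

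| Odds ratio of dropout per SD | Baseline shift | r | Bias in mean change | Share of 0.5 SD |
|---|---|---|---|---|
| 2 | −0.129 SD | 0.5 | (−0.5)(−0.129) = 0.064 SD | 13% |
| 3 | −0.186 SD | 0.5 | (−0.5)(−0.186) = 0.093 SD | 19% |
| 2 | −0.129 SD | 0.4 | (−0.6)(−0.129) = 0.077 SD | 15% |
| 2 | −0.129 SD | 0.6 | (−0.4)(−0.129) = 0.052 SD | 10% |

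The sign reverses if women with lower scores leave more often.

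**5. Bias against precision.** At r = 0.5 with equal SDs, the SD of change is √(2(1 − 0.5)) = 1 score SD, so steps 3 and 4 are in the same unit. The bias is 0.064/0.32 = 20% to 0.093/0.32 = 29% of the half-width.

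**6. Do the descriptive means escape this?** If the end point is the week 6 mean of those who answered minus the baseline mean of everyone, its bias is r × shift. At r = 0.5 and doubled odds that is 0.5 × (−0.129) = −0.064 SD: the same size, in the opposite direction.

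**7. Does the alternative help?** In simulation at r = 0.5 and doubled odds, a likelihood estimate using all baselines removed the bias. Its root mean squared error was 0.157 SD, against 0.171 SD for the completers' change. Under purely random dropout the figures were 0.153 and 0.157 SD. On these assumptions the change costs no accuracy when dropout is harmless.

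**The case against.** A reader might infer that the plan uses nothing but paired tests and yields no estimate of change. The article does not support that. The Abstract calls the analysis primarily descriptive, and Quantitative Analysis adds summaries at each time and regression models. Secondary Outcome makes the mean difference an end point. A point estimate is therefore planned; what is not stated is its interval. The descriptive summaries can also use every available score. The regressions are described too loosely to tell whether they would keep incomplete cases.

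A reader might also infer that the secondary estimate will be biased. Nothing in the article shows that dropout depends on baseline. Sample Size speaks of "considering a 20% potential dropout rate" without saying that it all falls after the first questionnaires, so some of the lost women may have no baseline score. Even on the assumed values the bias is well inside the sampling error. The article also disclaims any evaluation of effectiveness and has no control group.

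Missing-data handling is commonly left to a fuller protocol or analysis plan, so its absence here would be weak on its own. Finally, with complete pairs and two times, the mixed model reproduces the paired t result. Its gain is confined to women with one score, and it is a normal-theory method, whereas the plan chooses its test after checking assumptions.

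These objections limit the point but do not remove it. The article itself names complete-pair tests as the main tool and P≤.05 as the rule, and it ties progression to significance. Reminders and interviews may reduce or explain missing scores, but they do not bring an incomplete pair into the comparison.

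**Conclusion.** The point holds in limited form. The main pre-post inference rests on complete pairs and a significance rule. At the plan's own dropout figure about 10 of 50 women leave that inference, and the mean change named as an end point has no stated interval although it is meant to inform later trials. Power is barely affected (0.793 against 0.80). The possible bias is about 0.06 to 0.09 SD, conditional on dropout odds that double to triple per SD of baseline and a pre-post correlation of 0.5; it could take either sign or be absent. The mismatch between a P-value verdict and the stated planning aim needs no such assumption. The change is worth making because it is cheap, but the outcome is secondary and exploratory, and the sample size is not called into question.

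**What to change.** In Quantitative Analysis, for each questionnaire score measured before and after, estimate the mean change with a linear mixed model with time as a fixed effect and an unstructured covariance. Include every woman with a baseline score (week 0, or screening for the GHQ) or a week 6 score. Report the mean change with its 95% CI, the SD of change and the pre-post correlation. Keep the paired t, Wilcoxon and sign tests as sensitivity analyses.

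The cost is slightly more analysis work, in software the article already names, with no change to recruitment or data collection. The model relies on approximate normality and on dropout being explained by the observed scores. The retained nonparametric tests give some check on the first assumption. The second cannot be verified from the scores.

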#### Secondary Outcome

The variable expressing the “psychological well-being” outcome will be assessed by administering 6 self-report questionnaires at the beginning (ie, week 0) and the end (ie, week 6) of the module (refer to Table 1 for a detailed overview of the questionnaire adopted). The end points that will be measured are as follows: a score of the individual items of the questionnaires, the average score of the questionnaires, and the difference between the average score values of the individual questionnaires in the 2 survey times.

**Table 1 table1:** Summary of the questionnaires administered and their timing.

Questionnaires	Screening	At the beginning of the study (week 0)	At the end of week 3	At the end of the study (week 6)	Follow-up (2 months after birth)
K10^a^	✓				
GHQ^b^	✓			✓	
SF36^c^	✓				
PSS^d^		✓		✓	✓
MPFI^e^		✓		✓	
GSE^f^		✓		✓	
ERQ^g^		✓		✓	
COPE-NVI-25^h^		✓		✓	
UES-SF^i^			✓	✓^j^	
SUS^k^			✓	✓^j^	
ITA BUS B^l^			✓	✓^j^	
uMARS^m^				✓^j^	
Qualitative interview					✓

^a^K10: Kessler Psychological Distress Scale.

^b^GHQ: General Health Questionnaire.

^c^SF36: 36-Item Short Form Health Survey.

^d^PSS: Perceived Stress Scale.

^e^MPFI: Multidimensional Psychological Flexibility Inventory.

^f^GSE: General Self-Efficacy Scale.

^g^ERQ: Emotion Regulation Questionnaire.

^h^COPE-NVI-25: Coping Orientation to the Problems Experienced–New Italian Version (25-item).

^i^UES-SF: User Engagement Scale-Short Form.

^j^These usability questionnaires will be administered the following day, so as not to burden the participant during completion.

^k^SUS: System Usability Scale.

^l^ITA BUS B: Italian version of the Chatbot Usability Scale (version B).

^m^uMARS: User Mobile Application Rating Scale.

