These psychological instruments were selected for their widespread validation and adaptation in clinical and psychological research, as well as their relevance for assessing various aspects of mental health and coping in the context of digital health interventions. For example, the Kessler Psychological Distress Scale (K10) is a widely used screening tool for psychological distress, with strong validity across cultures, including Italian culture [45,46]. Furthermore, the Multidimensional Psychological Flexibility Inventory (MPFI) and the Perceived Stress Scale (PSS) are highly relevant for examining psychological flexibility and perceived stress, 2 critical constructs for understanding emotional and behavioral responses in mobile health contexts [47-49], (for detailed description of all questionnaires, refer to Step 3: Participation section).

In the framework of this study, these tools are adopted to assess early signals of potential effectiveness of the intervention while assessing UX and UE.

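### The sample size rests on a Bonferroni level of .025, but the analysis calls every result significant at P≤.05, and significance on unspecified psychological measures feeds the progression decision

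*Protocol article*

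**What the plan says.** **Sample Size (Methods).** For parametric tests, "the sample should consist of 41 pregnant women with Bonferroni correction (α=.025"; the nonparametric alternative gives 24 at the same α. The final recruitment figure of 50 is again tied to "a significance level of .025, and considering a 20% potential dropout rate". The hypothesis is two-sided ("alternative hypothesis (Ha):d≠d0"), with an expected difference of 1.0, an SD of the difference of 2.0 and power of 0.80. The section does not say which comparisons the correction covers.

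**Quantitative Analysis (Data Analysis).** Paired t, Wilcoxon and sign tests, regression models, McNemar and Cochran Q tests are listed. The only decision rule is "For each analysis, statistical significance will be found with a *P* value of ≤.05". No multiplicity correction appears.

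**Secondary Outcome.** Psychological well-being is measured by six questionnaires before and after the intervention. The end points are "a score of the individual items of the questionnaires, the average score of the questionnaires" and the change in average score between the two times. Table 1 and the Step 3 overview show five questionnaires at week 0 and six at week 6, because the GHQ is given at screening and week 6.

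**Results.** Significant improvement in psychological measures is listed as a feasibility benchmark, alongside engagement, retention and dropout, and feedback on acceptability and usability. If the benchmarks are achieved, the work moves to a broader trial.

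**The concern.** A test cannot be governed by two thresholds. A result with P=.04 counts as significant under the analysis section but not under the level that justified the sample size. The article fixes a value in both places, so this is not a detail left to an analysis plan.

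The number of tests does not match either. A Bonferroni level of .025 is .05/2 and protects two comparisons, whereas the secondary outcome has six questionnaires. At stake is the progression decision: with no required measures named, any of the six could be cited as the improvement that meets the benchmark.

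**Working it through.** **1. Reproduce the plan's sample size.** Inputs from the Sample Size section: difference 1.0, SD of difference 2.0, two-sided test, power 0.80. Standardised effect d = 1.0/2.0 = 0.5. Paired t test, power from the noncentral t distribution with n−1 degrees of freedom and noncentrality d√n:

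| Two-sided α | Smallest n with power ≥0.80 | Power at that n | Power at n=41 |
|---|---|---|---|
| .025 | 41 | 0.805 | 0.805 |
| .05 | 34 | 0.808 | 0.878 |

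The stated 41 reproduces at two-sided .025. A one-sided .025 also gives 34. So .025 is not a slip in the text; it set the sample size. Using .05 in the analysis raises power from 0.805 to 0.878 at n=41. The figure of 24 cannot be checked, because no effect is given for the Noether formula.

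**2. What .025 protects.** For k independent tests with no true change, the chance of at least one significant result is 1 − (1−α)^k.

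- Two tests at .025: 1 − 0.975² = 4.9%.
- Two tests at .05: 1 − 0.95² = 9.75%.

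**3. What the analysis rule gives.**

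- Six questionnaire scores at .05: 1 − 0.95⁶ = 26.5%.
- Five scores (GHQ left out, since it is not given at week 0): 1 − 0.95⁵ = 22.6%.
- Six scores that are positively correlated: about 24% at a common correlation of .3 and 21% at .5. These correlations are assumptions; the article gives none.

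**4. The error relevant to the benchmark.** The benchmark concerns improvement, and a two-sided test at .05 puts .025 in that direction. At least one false improvement among six independent scores: 1 − 0.975⁶ = 14.1%. Positive correlation lowers this, to roughly 8% at an assumed correlation of .7.

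**5. Would changing .05 to .025 be enough?** Six two-sided tests at .025: 1 − 0.975⁶ = 14.1%. The expression is the same as in step 4, but it now counts changes in either direction. Aligning the threshold removes the contradiction without giving 5% over six scores, because .025 covers only two tests.

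**The case against.** The strongest reply is that little turns on this. The primary outcomes are user experience and engagement. The Secondary Objective section says the pre-post comparison is not an efficacy evaluation, the Discussion accepts that change may not be due to the intervention, and the abstract describes the analysis as mainly descriptive. Exploratory tests at .05 are ordinary practice. All of this stands and lowers the severity. It does not remove the conflict, because the plan itself chose a corrected level and also attached significance to a progression benchmark.

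Several stronger readings are tempting but not supported:

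- **That the plan promises 5% family-wise error.** Bonferroni appears only in the sample-size paragraph. Control in the analysis is implied there and nowhere declared.
- **That item-level testing adds many more false positives.** Item scores are listed as end points, but the change end point is defined on average scores, and nowhere does the article say that each item is tested.
- **That 26% is the risk of moving forward by chance.** It includes significant worsening, and psychological improvement is one benchmark among several.
- **That the mismatch leaves the study underpowered.** Power rises at .05.
- **That the two protected comparisons must be the PSS and MPFI.** The Secondary Outcome section calls these constructs "2 critical constructs for understanding emotional and behavioral responses in mobile health contexts", but in explaining the choice of instruments, not in ranking end points. The factor of 2 is not tied to any two end points; the same paragraph mentions Wilcoxon post hoc tests, so it could refer to those.

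**Conclusion.** The point holds as an inconsistency that should be fixed. The sample size was derived at two-sided .025, and the analysis declares significance at .05 without correction. Under no true change, six questionnaire scores give at least one significant result about 26% of the time if independent, 23% for five scores, and about 21% to 24% for six scores at assumed correlations of .5 to .3. At least one false improvement occurs about 14% of the time if independent. These figures assume one test per questionnaire score. A further limit is that the GHQ is also an entry criterion (score ≥3), so a screening-to-week-6 comparison can shift through regression to the mean, which no α rule corrects. The issue is material because the progression benchmark refers to significance and names no required measures; the secondary, exploratory status keeps it short of critical.

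**What to change.** Use one α rule in the Sample Size and Quantitative Analysis sections. Either of two routes is sound:

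1. **Keep the correction.** The sponsor names in advance the two pre-post comparisons to be tested, each at P≤.025, and replaces the general .05 sentence. The benchmark in the Results section is tied to those two. All other scales, and any item results, are reported as estimates with 95% confidence intervals and no significance claim. Which two comparisons is the sponsor's choice.
2. **Drop the correction.** Remove the Bonferroni wording, restate the basis of the sample size, declare all pre-post tests exploratory, and base the benchmark on estimates with confidence intervals instead of significance.

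The cost is a few sentences. Under route 1 no extra participants are needed on account of this change. The downside of either route is that fewer results can be called significant.
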